**Questionnaires**							
PGIC	✓		✓		✓	✓	✓
APAQ	✓		✓		✓	✓	✓
FSS	✓		✓		✓	✓	✓
HADS	✓		✓		✓	✓	✓
PCS	✓		✓		✓	✓	✓
Pittsburgh	✓		✓		✓	✓	✓
**Accelerometry**	✓		✓		✓	✓	✓

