### Sample Size

Population size is calculated on an expected difference of 20% of the level of MVPA (≥3 METs for metabolic equivalent tasks). Estimating that at baseline, patients are at 3.9 MET-h/week with a standard deviation between 2 and 4 (40), for an alpha risk of 5% and a potency set at 90%, we need to include 150 patients per group; adding an expected dropout rate of 10%, it is necessary to include 165 patients per group to meet the main goal, which means a total of 330 patients.

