### Statistical Analysis

The included population will first be described globally and in groups (test or control), the comparability of the groups will be verified. For quantitative variables, Student's *T*-tests or rank tests (in case of non-normal distribution) will be implemented. The normality of the variables will be checked beforehand with a Shapiro-Wilk test. For qualitative variables, chi-square or Fisher-exact tests (if theoretical numbers are insufficient) will be used. The results will be considered significant at the 5% threshold. The analysis will be carried out in intent-to-treat. An analysis of the main endpoint will be done per protocol. Patients who do not perform 85% of the exercises will be excluded from per-protocol statistical analysis. In addition, we will lead a qualitative study through semistructured individual interviews conducted by a sport and health sociologist. Thirty patients will be recruited in each of the two groups (41, 42). A full transcript will be followed by a thematic and comparative analysis of the cross-data content.

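### The tests named for the 1-year accelerometry endpoint use one visit only, although accelerometry is scheduled at V1 to V5 and 10% dropout is expected

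*Protocol article*

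**What the plan says.** All references are to the protocol article.

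- **Statistical Analysis.** The population is fixed by "The analysis will be carried out in intent-to-treat". A per-protocol analysis of the main endpoint is added, and the section's only exclusion rule belongs to it: "Patients who do not perform 85% of the exercises will be excluded from per-protocol statistical analysis".
- **Statistical Analysis, tests.** Quantitative variables get Student's t-tests, or "rank tests (in case of non-normal distribution) will be implemented". For qualitative variables, "chi-square or Fisher-exact tests (if theoretical numbers are insufficient) will be used". The tests are assigned by type of variable. No other between-group comparison is named for the primary endpoint.
- **Assessment Measures.** The primary outcome is a 7-day accelerometry mean at 1 year. The same section also expresses success as at least 7.5 MET-h/week at that time. Accelerometry further serves the secondary lifestyle objective (activity and sedentary time).
- **Sample Size.** The target is an "expected difference of 20% of the level of MVPA", from a baseline of 3.9 MET-h/week with an SD between 2 and 4. This leads to 150 per group and then, "adding an expected dropout rate of 10%, it is necessary to include 165 patients per group to meet the main goal".
- **Table 2.** The row "Accelerometry" is ticked at V1, V2, V3, V4 and V5.

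**The concern.** Each named test takes one value per patient at one time. Applied to the 1-year endpoint, it leaves four scheduled recordings per patient out of the primary comparison. It also has nothing to work with when V5 is missing, unless a value is assigned first.

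This matters because loss in this trial may well be related to the outcome. The outcome is itself sustained activity, so a patient who gives up activity and leaves is doing badly on the endpoint. The trial is open-label, and the arms ask for different things: supervised hospital sessions followed by a community relay in one, advice for practice at home in the other, with the same education sessions in both. Reasons for leaving could therefore differ by arm. If they do, a comparison of observed V5 values does not estimate the difference among all randomised patients. Earlier recordings from patients who later leave carry information about them that the stated tests discard.

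**Working it through.** **1. The plan's own dropout step.** 150 × 1.10 = 165 per group, and 2 × 165 = 330; both reproduce. Dividing instead gives 150 / 0.90 = 166.7, so 167, which is 2 more per group and of no consequence. At 10% loss, 165 × 0.90 = 148.5 per group have a V5 recording, and 0.10 × 330 = 33 patients in total do not.

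**2. The target difference.** Reading the 20% as relative to baseline: 0.20 × 3.9 = 0.78 MET-h/week. (At two-sided 5% and 90% power, 150 per group is returned only at an SD of about 2.08, near the bottom of the stated range. That is a separate matter; 0.78 serves here only as a yardstick.)

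**3. Bias if only observed V5 values are compared.** In one arm, let p be the share lost, M_c the mean of those observed and M_d the mean that those lost would have had.

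- Mean of all randomised = (1 − p) × M_c + p × M_d
- Observed mean minus mean of all = p × (M_c − M_d) = p × d
- Bias in the difference, test minus control = p_T × d_T − p_C × d_C

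**4. Illustration A (assumed).** 10% lost in one arm, those lost 1 SD less active than those observed, and no outcome-related loss in the other arm.

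| SD (MET-h/week) | Bias = 0.10 × SD | Share of 0.78 |
|---|---|---|
| 2 | 0.2 | 26% |
| 3 | 0.3 | 38% |
| 4 | 0.4 | 51% |

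If the arm is the test arm, the effect is overstated. If it is the control arm, the effect is understated by the same amount.

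**5. Illustration B (assumed).** 15% lost in one arm and 5% in the other, with the same deficit d in both.

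- d = 0.78: 0.15 × 0.78 − 0.05 × 0.78 = 0.078, or 10% of 0.78
- d = 2: 0.15 × 2 − 0.05 × 2 = 0.20, or 26% of 0.78

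**6. Equal losses.** If p and d are the same in both arms, p × d − p × d = 0.

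**7. What cannot be computed.** The precision gained by adding V1 to V4 depends on the correlation between visits, which the article does not give.

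**The case against.** A reader might infer that the primary result is a completer analysis and that the intent-to-treat label is therefore wrong. The documents do not support that, for four reasons.

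- The article sets no exclusion for the intent-to-treat analysis. Its 85% rule applies to the per-protocol set only, which suggests that low adherers stay in the main analysis. Table 2 puts no adherence condition on V5 accelerometry.
- A dropout allowance protects precision. It does not define the analysis set and does not contradict intent-to-treat.
- A t-test or chi-square can follow imputation. For the 7.5 MET-h/week status, counting missing as not reached keeps every randomised patient.
- A missing-data rule is commonly left to the full protocol or SAP, neither of which is shown. Its absence from an article is no finding.

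All four stand. Two other tempting statements also go too far. The V2 to V4 recordings are not unused, because they are available to the secondary lifestyle objective; what is true is that they have no stated role in the primary comparison. Nor does the article support assuming that outcome-related loss falls on the test arm alone. The 51% figure is an extreme case: with a test-arm mean of 1.2 × 3.9 = 4.68 and an SD of 4, those lost would average 4.68 − 4 = 0.68 MET-h/week, close to no activity of this intensity.

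It can also be said that a landmark comparison at 1 year is legitimate and that a mixed model assumes data missing at random, which loss due to inactivity may violate. Both are fair. The mixed model also adds little for patients lost early. These points explain why a sensitivity analysis is needed; they do not favour ignoring the recordings already made.

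**Conclusion.** The point holds as an improvement to a stated choice. For an endpoint scheduled at five visits, with 10% loss expected, the article names only single-timepoint two-sample tests. As stated, these use neither the baseline nor the V2 to V4 recordings, and they leave a patient without V5 with no contribution unless a rule elsewhere supplies a value. It is not shown that such patients are excluded or that the analysis departs from intent-to-treat.

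The size depends on assumptions that the article does not settle. Possible bias runs from zero (losses alike in both arms), through 0.08 to 0.20 MET-h/week (15% against 5% loss), to 0.2 to 0.4 (10% in one arm only, 1 SD less active, SD 2 to 4). The sign may go either way. The change should be made because it is cheap and protects the primary result, not because the present plan is demonstrably invalid.

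**What to change.** - **Primary analysis, continuous MET-h/week.** Use a longitudinal mixed model on all randomised patients with at least one recording, with V1 to V5 as outcomes, a common baseline mean, arm by visit terms and an unstructured covariance. The V5 contrast between arms is the primary result.
- **Sensitivity analysis for data not missing at random.** Set missing test-arm V5 values to the patient's own baseline level. For the 7.5 MET-h/week status, count missing as not reached.
- **Confirm in the SAP** how patients without a V5 recording enter the intent-to-treat analysis, and that V5 accelerometry is sought from patients who have stopped the sessions.

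The cost is SAP wording and modest extra programming; no new measurement is needed. The model assumes data missing at random, which the sensitivity analysis probes but cannot verify. No gain in precision should be promised in advance, because no between-visit correlation is given.

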## Discussion

This study aims to evaluate the efficacy of an optimized care organization within the Loire Territory Hospital Group, illustrated by the sustainability of therapeutic adherence of FM patients. This interventional research will allow us to assess the evolution of behaviors in physical activity after a FM syndrome management based solely on patient education or based on a supervised and adapted practice of physical activity associated with this same therapeutic education program.

Supervised exercise allows a better participation and adhesion to physical activity in sedentary women (43) and an improvement in psychological well-being determined by the result of HADS in FM (44). Improvements up to two times greater than those of unsupervised training can be observed, however without necessarily being maintained for the long-term at 1 year (45). A recent study has explored the experience of the transition from a supervised exercise in the hospital to a community-based unsupervised program in prostate cancer patients, emphasizing the importance of a structured, accompanied and over time monitored relay (46). Dnes et al. (47) identified the barriers and facilitators to participating in community-based exercise opportunities from the perspective of adults with chronic pain, including FM. The main factors identified were participation in groups with similar levels of capabilities, delivered by an instructor able to tailor exercises to chronic pain and recommended by their healthcare provider. Also, in this project, the implementation of physical activity in community programs, chosen by the patient himself/herself according to his/her preferences and availability, could strengthen the integration of physical activity into daily life through the connection with the sports health centers, which have the role of labeling the health-sports club, with groups specific to chronic pathologies delivered by trained instructors.

The combination of education and physical activity demonstrated its efficacy on management of several FM symptoms. However, the level of physical activity practice in the short-term after the intervention and at the long-term at 1 year has been barely studied. Physical activity monitors are interesting tools to better understand the role of physical activity in rheumatic disease populations (48). For example, the use of a pedometer to measure the activity in FM patients after a multidisciplinary intervention based on cognitive behavioral therapy and physical therapy demonstrated an increase in exercise capacity and regularity (49). Others studies evaluated the physical activity behavior in FM patients compared to healthy subjects, and the link between their behavior and their symptoms (40, 50). However, to our knowledge, no study has evaluated the impact of its intervention on objective data for measuring physical activity and sedentary behavior *via* accelerometry among FM patients.

Qualitative analysis of the project will provide data for evaluation of the acceptability and the feasibility of our intervention, according to the patients' experiences. This analysis will allow us to better understand the barriers and facilitators that can be used to design an intervention more suited to the expressed needs of the participants.

To conclude, the multidisciplinary management proposed must contribute to the construction of a solid therapeutic alliance between the patient and the management of its FM syndrome and thus give the initial medical prescription of APA the appearance of a therapeutic project. It is also a question of strengthening the city–hospital link by (1) developing an optimal care sector, (2) which combines therapies validated by scientific societies, (3) including APA that we wish to place at the center of a multidisciplinary and consensual care organization, and (4) which relies on existing and efficient structures for many chronic pathologies, with (5) an objective of sustainability within the largest national territory hospital group.

## Ethics Statement

The protocol is in accordance with ethical principles established by the 18th World Medical Assembly (Helsinki 1964) and was approved by the institutional review board (CPP Sud-Méditerranée II, France). Each patient will be awarded an information notice explaining the study and must sign an informed consent form before being able to participate in the research.
